# Source Documents and Access to Source Data/Documents

Appropriate medical and research records will be maintained for this trial, in compliance with ICH E6 GCP, Section 4.9 and regulatory and CVD requirements for the protection of confidentiality of subjects. Study investigators and the clinical coordinator will have access to all study records. Study nurses and clinicians will have access to laboratory source documents and CRFs of participants who are being actively enrolled and followed. Laboratory staff will have access to laboratory source documents. Data entry clerks and the Data Manager will have access to anonymized CRFs. Authorized representatives of DMID will be permitted to examine (and when required by applicable law, to copy) clinical records for the purposes of quality assurance reviews, audits and evaluation of the study safety and progress.

Standard case record forms (CRF) will be provided for each participant. Participants will be identified by the Participant Identification Number (PID). All data on the CRF will be recorded in black ink legibly. A correction will be made by striking through the incorrect entry with a single line and entering the correct information adjacent to it. The correction will be initialed and dated by the individual who makes the change. Any requested information that is not obtained as specified in the protocol should have an explanation noted on the CRF as to why the required information was not obtained.

The central source document will be the CRF, which includes history, physical examination, laboratory data, and diagnosis as determined by a study physician. This document will be completed for all participants. Termination forms will be recorded for all participants who leave the study, indicating the reason for exit. Laboratory tests will be labeled with PIDs. Results from the laboratory at the Health Centre and at Queen Elizabeth Hospital will be recorded in laboratory source books. The results will also be given to the clinicians for review and to record in the CRF. The original documentation of laboratory results will be kept in the participant’s file.

# Quality Control and Quality Assurance

Standard operating procedures (SOPs) will be in place for quality management including how the data will be evaluated for compliance with protocol, which documents will be reviewed and methods of training staff.

The study will be conducted at a single center, the Blantyre Malaria Project Research Clinic at Ndirande Health Centre in Blantyre, Malawi.

Site monitoring will be conducted by a DMID contractor to assure protocol compliance, ethical standards, regulatory compliance and data quality.

Following written SOPs, the monitors will verify that the clinical trial is conducted and data are generated, documented (recorded), and reported in compliance with the protocol, GCP, and the applicable regulatory requirements. Reports will be submitted to DMID on monitoring activities.

We will provide direct access to source data/documents, and reports for the purpose of monitoring and auditing by the sponsor, and inspection by local and regulatory authorities.

The EMMES Corporation will implement quality control procedures beginning with the data entry system and generate data quality control checks that will be run on the database. Any missing data or data anomalies will be communicated to the site for clarification/resolution.

# Ethics/Protection of Human Subjects

## Ethical Standard

The investigator will ensure that this study is conducted in full conformity with the principles set forth in The Declaration of Helsinki and according to the US national requirements codified in 45 CFR 46, 21 CFR 50&56 and consistent with ICHE6(R1).

## Institutional Review Board

This protocol, the informed consent document and any subsequent modifications will be reviewed and approved by the Institutional Review Board or Ethics Committee responsible for oversight of the study including the University of Malawi College of Medicine Research and Ethics Committee (COMREC), University of Maryland and Michigan State University. All of these IRBs hold valid US Federalwide Assurances from OHRP. COMREC will be the IRB of record for this study. Any amendments to the protocol or consent materials must be approved by all three IRBs before they are implemented.

## Informed Consent Process

Informed consent is a process that is initiated prior to the parents/guardians agreeing to their children’s participation in the study and continuing throughout the individual’s study participation. Discussion of risks and possible benefits will be provided to the family of the participants. Consent forms describing in detail the study interventions, procedures and risks are given to the parents/guardians. Written informed consent will be obtained from the parent/guardian prior to screening and enrollment. A copy of the consent forms will be given to the parent/guardian. Consent forms will be available in both English and Chichewa, the local language. Consent forms will be IRB-approved and the parent/guardian will be asked to read and review the document. For participants who cannot read, the complete document will be read aloud to them. Upon reviewing the document, the investigator will explain the research study to the parent/guardian and answer any questions that may arise. The parent/guardian will be asked to sign and date the informed consent document after he/she has had sufficient time to make a decision. Those who cannot write their names will be asked to indicate their consent with a thumbprint. An impartial witness should observe this process, in the case of the use of a thumbprint in place of a signature, and sign and date the informed consent document. If no impartial witness is available, a member of the study staff other than the person administering consent may serve as a witness and sign the document. The parent/guardian may withdraw consent at any time throughout the course of the trial. Any use of the study samples that is outside the scope of the objectives of this protocol will be submitted as a new protocol to all participating IRBs.

### Informed Consent/Assent Process (in Case of a Minor)

Assent will not be obtained as the participants will all be under the age of 6 years.

## Subject Confidentiality

Subject confidentiality is held in strict trust by the investigators, the staff and the study sponsor. This confidentiality is extended to cover testing of biological samples in addition to the clinical information relating to participants. The study protocol, documentation, data and all other information generated will be held in strict confidence. No information concerning the study or the data will be released to any unauthorized third party without prior approval of the sponsor.

The study monitor, regulatory authorities, IRBs or other authorized representatives of the sponsor may inspect all documents and records required to be maintained by the investigator, including but not limited to, medical records and pharmacy records. The clinical study staff will permit access to such records.

## Study Discontinuation

If the study is discontinued, participants who have not completed the three days of therapy for an episode of malaria will be given the first line malaria treatment that complies with national guidelines in Malawi. Participants will be referred to the Ndirande Health Centre or Queen Elizabeth Central Hospital for any further medical concerns.

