# Background Information and Scientific Rationale

## Background Information

In 1993, Malawi was the first sub-Saharan African country to discontinue the routine use of chloroquine and to elevate the antifolate combination sulfadoxine-pyrimethamine (SP) to the antimalarial of first choice nationwide. The decision was based on chloroquine's increasing failure to produce adequate clinical and hematological recovery (1). Since 1993 SP has been the only available treatment for uncomplicated malaria in all government health facilities, and is dispensed without prescription. Although chloroquine has remained available by prescription and through unauthorized private sources, a national information campaign was largely successful in convincing health practitioners and the public to accept SP as the treatment of choice for children with malaria.

It has been speculated that years of reliance on antimalarials other than chloroquine might lead to the reemergence of chloroquine-sensitive *P. falciparum* and permit the reintroduction of this safe and affordable drug. We retrospectively measured the prevalence of the *pfcrt* 76T molecular marker for chloroquine-resistant *P. falciparum* malaria in Blantyre, Malawi. From 1992 to 2000, we documented a gradual decrease in prevalence of the mutation associated with chloroquine resistance (2) and neither we nor other investigators have found any parasites with the mutation since 2001 ([name], personal communication and [name], personal communication).

We have demonstrated the clinical efficacy of chloroquine, as well. In preparation for the present study, we conducted a trial to assess the efficacy of chloroquine in treating children with uncomplicated malaria at the Blantyre Malaria Project Research Clinic at the Ndirande Health Centre from May through December, 2005. Two hundred ten children with uncomplicated malaria were randomly assigned to receive either SP, the standard therapy in Malawi, or chloroquine. Among 105 children randomized to receive chloroquine monotherapy, only one experienced treatment failure. The results are shown in Table 1. Based on these results, we have determined that chloroquine is safe to use to treat malaria in this population.

|  | Chloroquine | SP |
| --- | --- | --- |
| Adequate clinical and parasitologic response (% per-protocol) | 79 (99) | 16 (18) |
| Early treatment failure (% per-protocol) | 1 (1) | 21 (24) |

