| Late clinical or parasitologic failure (% per-protocol) | 0 (0) | 50 (57) |
| Outcomes unknown | 25 | 18 |
| Total | 105 | 105 |

Table 1: Outcomes of 28-day efficacy study of chloroquine vs. SP for the treatment of uncomplicated malaria among children in Blantyre, Malawi.

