# Study Design

## Study site

Ndirande is a peri-urban hillside township adjacent to Blantyre, the largest city in Malawi. Accurate census data are not available for Ndirande, but the population is approximately 200,000. Malaria transmission is year-round, with a seasonal peak from December to March corresponding to the rainy season. The Ndirande Health Centre is the sole government health facility serving the entire township, and consists of a complex of buildings with outpatient clinics and a maternity center. Our field team of clinicians, nurses and technicians has been conducting malaria drug efficacy studies at the Health Centre continuously since 1997 and has an excellent relationship with the community. During this time more than 3,000 participants have been enrolled in five studies, including clinical trials and longitudinal studies. After operating in dedicated space within the Centre facility for several years, in 2002 we established a new research facility on the Centre grounds. The Blantyre Malaria Project Research Clinic contains rooms for clinicians and nurses, laboratory space for the microscopists, a dispensary, an administrative office, a conference room and a computer room for real time data entry. We maintain a close relationship with the Ndirande Health Centre government workers. When we provide diagnosis and treatment in the context of our clinical studies, we offer relief from overcrowded conditions in the Centre. Back-up clinical and laboratory support is available a 10 minutes drive from the Centre at the pediatric research ward in Queen Elizabeth Central Hospital.

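### Section 14.5 moves every child who is mid-course at study discontinuation to the national first-line drug, which until the policy changes is SP, a drug the protocol itself reports as poor

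*Protocol*

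**What the plan says.** Protocol section 14.5 (Study Discontinuation) provides that, if the study is discontinued, participants who have not completed three days of therapy "will be given the first line malaria treatment that complies with national guidelines in Malawi". It names no drug, makes no exception by reason for stopping, and does not let the child finish the assigned course. It continues: "Participants will be referred to the Ndirande Health Centre or Queen Elizabeth Central Hospital for any further medical concerns".

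Background Information identifies the national treatment. Malawi's 1993 decision was "to elevate the antifolate combination sulfadoxine-pyrimethamine (SP) to the antimalarial of first choice nationwide", and "Since 1993 SP has been the only available treatment for uncomplicated malaria in all government health facilities". Known Potential Benefits says that the policy is being revised because SP works poorly, that no new regimen has been announced, and that implementation is unlikely before late 2007. The Rescue therapy text under section 7.3 adds that an artemisinin-based combination is being selected.

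Table 1 in Background Information reports the 2005 trial of chloroquine against SP at the same clinic, with 105 children per arm. Section 5.4.5 lets the sponsor terminate the study at its discretion.

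**The concern.** A discontinuation need not concern safety or efficacy, since section 5.4.5 leaves it to the sponsor. Suppose the study stopped for an administrative reason before the national policy changed. A child on day 1 or 2 of an observed, chloroquine-based course would then be switched to SP. Known Potential Benefits lists treatment with an effective antimalarial as a benefit of taking part, and section 14.5 would end it partway through a course.

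The onward referral gives only partial protection. "The Ndirande Health Centre is the sole government health facility serving the entire township", and by the Background text SP is the only treatment for uncomplicated malaria in such facilities. The hospital is the other place named, and the protocol does not say what it would give for uncomplicated malaria.

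What is at stake is the care of a few children at the end of the study. No trial estimate depends on section 14.5.

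**Working it through.** **1. Reproduce Table 1.** The per-protocol denominator is adequate response + early failure + late failure.

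- SP: 16 + 21 + 50 = 87, and 87 + 18 unknown = 105. Adequate response 16/87 = 18.4% (exact 95% CI 10.9 to 28.1%). Early failure 21/87 = 24.1%.
- Chloroquine: 79 + 1 + 0 = 80, and 80 + 25 unknown = 105. Adequate response 79/80 = 98.75% (93.2 to 99.97%). Early failure 1/80 = 1.25%.

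These match the table's rounded 18% and 99%. The difference in adequate response is 98.75 − 18.4 = 80.4 percentage points.

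**2. Could the unknown outcomes explain the gap?** The table gives "Outcomes unknown | 25 | 18" (chloroquine, then SP). Count every SP unknown as a success and every chloroquine unknown as a failure:

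- SP: (16 + 18)/105 = 34/105 = 32.4%
- Chloroquine: 79/105 = 75.2%

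The gap is still 42.9 points, so missing outcomes do not account for it.

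**3. What has a mid-course child already received?** The dosing schedule is 10, 10 and 5 mg/kg on days 0, 1 and 2, a total of 25 mg/kg. After one dose the child has had 10/25 = 40% of the chloroquine, and after two doses 20/25 = 80%. The Pharmacokinetics table gives chloroquine a half-life of 7 to 10 days. In three of the four arms the child has also been assigned a partner drug. The 18.4% in step 1 is for SP as the only drug, so it does not apply directly to these children.

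**4. How many children could be mid-course on a given day?** Assumptions:

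- the design rates in section 11.2: 1.5 episodes per year on monotherapy and 1.0 on each combination, plus the enrolment course, giving 2.5 and 2.0 courses per child;
- 120 to 160 children per arm followed for a year;
- a study lasting 2 to 2.5 years (730 to 913 days);
- 2 to 3 days mid-course per treatment.

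Total courses:

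- Low: 120 × 2.5 + 360 × 2.0 = 1,020
- High: 160 × 2.5 + 480 × 2.0 = 1,360

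Mid-course on an average day = courses × days per course ÷ study days:

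- Low: 1,020 × 2/913 = 2.2
- High: 1,360 × 3/730 = 5.6

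This gives about 2 to 6 children. It is an average over the study and takes no account of season or of the pace of enrolment.

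**The case against.** Section 14.5 follows whatever guideline is in force on the day, and the protocol expects that guideline to move to an artemisinin combination. No start date is given. Harm needs a full discontinuation, before the policy change, for a reason other than safety or efficacy. Returning children to national policy when a trial ends is also a defensible default, and if regulators halt dosing the site cannot simply continue. All of this stands, and it limits the point to a small one. It does not remove it, because until the change section 14.5 still switches a responding child to SP.

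Three stronger readings are tempting and are not supported.

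- *Only about 18% of switched children would be cured.* The contrast in Table 1 is between full single-drug courses. The documents give no outcome for partial chloroquine followed by SP. Applying SP's early-failure rate to step 4 gives 2.2 × 0.241 = 0.5 to 5.6 × 0.241 = 1.3 early failures. Those are upper-end values that ignore the chloroquine already taken.
- *The rescue-therapy text (sections 6.7, 7.3 and 8.2) has the same fault and should bar SP.* Those sections defer to national guidelines after treatment failure, intolerance or severe malaria. The protocol does not show which drug the guidelines give after a failure, so no fault is shown there.
- *Atovaquone-proguanil should be named as the replacement.* It did well in the paediatric studies cited under Efficacy. However, the protocol says that its combination with chloroquine had not been studied in vivo. The choice belongs to the clinical leads.

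**Conclusion.** The point holds as a minor patient-safety correction to one sentence. The rule makes no distinction by reason for stopping. The drug it pointed to when written was SP, and the protocol's own data show SP to be much worse than chloroquine at this clinic (18.4% against 98.75% adequate response, or 32.4% against 75.2% with the unknown outcomes counted against the claim).

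Under the assumptions in step 4 about 2 to 6 children would be mid-course on an average day. The number affected is nil if the study never stops early, or stops after the policy has changed. The size of the harm per child cannot be derived from the documents, and no trial result is affected.

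**What to change.** In section 14.5, replace the rule for mid-course children with wording to this effect: children who are mid-course at discontinuation complete their assigned three-day course under direct observation, unless the study or their arm is stopped for safety or poor efficacy, or regulators or ethics committees do not allow further dosing. In those cases they receive an effective antimalarial chosen by the clinical leads, and not SP while SP is still the national first-line drug.

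The cost is at most two more supervised doses per child, plus sponsor and ethics-committee agreement to the wording, since the study runs under an IND. No extra participants and no change to the analysis are needed.

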## Future Use of Stored Specimens

Filter paper specimens, cryopreserved parasites and serum will be maintained after the study is complete if the parent/guardian has agreed to this storage during the informed consent process and indicated permission on the written document. Any analysis of these specimens that is outside the scope of the objectives of this protocol, including human genetic analysis, will be submitted for prior review and approval by the appropriate IRBs. Parasites and their genetic material may be delinked for further analysis, without any identifying clinical information.

# Data Handling and Record Keeping

The principal investigator is responsible to ensure the accuracy, completeness, legibility and timeliness of the data reported. All source documents will be completed in a neat, legible manner to ensure accurate interpretation of data. Black ink is required to ensure clarity of reproduced copies. When making changes or correction, the original entry will be crossed out with a single line and the change will be dated and initialed. Records will be kept in locked files.

## Data Management Responsibilities

All source documents and laboratory reports will be reviewed by the study team and data entry staff, to ensure that they are accurate and complete. Adverse events must be graded, assessed for severity and causality, and reviewed by the PI, an investigator, or the clinical coordinator. Data collection is the responsibility of the clinical trial staff at the BMP-Ndirande Research Clinic under the supervision of the clinical coordinator and the investigators. During the study, the investigator must maintain complete and accurate documentation for the study. The EMMES Corporation will serve as the Statistical and Data Coordinating Center for this study and will be responsible for the data management, quality review, analysis, and reporting of the study.

## Data Capture Methods

Clinical and laboratory data will be collected on case report forms and entered into a 21 CFR Part 11-compliant web-based database system designed by EMMES. The data system includes password protection and internal quality checks to identify data that appear inconsistent, incomplete or inaccurate.

## Types of Data

The types of data for this study include clinical outcomes, safety parameters and molecular analyses.

## Timing/Reports

The DSMB will decide the appropriate time for the interim analysis. The report will be produced that will include safety and efficacy. Safety data will be presented as line lists of SAEs with descriptions and relatedness to study drug as well as tallies of grade 3 and 4 AEs by treatment arm. Efficacy data will be presented as 28-day clinical treatment outcomes.

## Study Records Retention

Study documents will be retained for a minimum of 5 years after completion of the study. No formal marketing applications are expected to result from this study. No records will be destroyed without the written consent of the sponsor.

## Protocol Deviations

A protocol deviation (PD) is any noncompliance with the clinical trial protocol, Good Clinical Practice (GCP), or protocol-specific Manual of Procedures requirements. The noncompliance may be either on the part of the subject, the investigator, or the study site staff. As a result of deviations, corrective actions are to be developed by the site and implemented promptly.

These practices are consistent with Good Clinical Practice:

4.5 Compliance with Protocol, sections 4.5.1, 4.5.2, and 4.5.3

5.1 Quality Assurance and Quality Control, section 5.1.1

5.20 Noncompliance, sections 5.20.1, and 5.20.2.

It is the responsibility of the site PI/study staff to use continuous vigilance to identify and report deviations within 5 working days of identification of the PD. All protocol deviations will be addressed in study subject source documents. Protocol deviations forms will be completed by the clinical coordinator or another investigator and inputted into the data entry system and reported on a weekly basis by EMMES. A completed copy of the Protocol Deviation Form must be maintained in the Regulatory File, as well as in the subject’s source document. Protocol deviations must be sent to the local IRB/IEC per their guidelines. The site PI/study staff is responsible for knowing and adhering to their IRB requirements.

